### **5.3 Missing data**

Five patients have no online baseline assessment (technical problems). For the primary analysis these missing baseline BDI-II scores will be replaced by a regression imputation with the MADRS scores which were collected paper based. Although the mixed model described above is robust to a certain extent to missing data, sensitivity analyses will be performed as supporting analyses (see section 5.2).

### **5.4 Harms**

Adverse events will be summarized as frequencies and percentages by intervention group. New occurrence of suicidal ideation or intent as well as worsening of depressive symptoms above the clinical threshold are considered as potential adverse events. Every AE fulfilling one of the following criteria is a SAE:

- Suicidal ideation or intent (as measured by a score of 3 on BDI-II item 9 at any assessment, during the clinical interview at V2 or spontaneous report in a web message to the therapist or by contacting the study site)
- Hospitalization due to psychiatric disorder classified according to ICD10 or DSM5
- Lethal or life-threatening (incl. suicide or suicide attempt).

However, the intervention is generally considered low risk as Deprexis has been used in numerous clinical trials without evidence for adverse events and is categorized as a “low risk” medical device according to its German CE®-certification.

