### Introduction

This manual is intended for “therapists” participating in the IDEMS trial (<https://clinicaltrials.gov/ct2/show/NCT02740361>). In the context of this study, the term “therapists” refers to study personnel involved in providing web message support to participants in the respective condition of the trial. The main tasks of these therapists will be to use the online study platform to (1) send weekly messages to participants and (2) respond within three days to any web-messages they receive from participants.

This manual was based, in part, on a previous manual developed by [name] in the context of another study in which e-mail support was provided for Deprexis. As described in the IDEMS study protocol, the e-mail support will generally follow procedures used by Berger et al. (2011).

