## **2.7 Timing of Outcome Assessments**

Outcomes are measured at week 0 (baseline) and week 12 when visiting the clinic. In addition, BDI-II outcomes are measured at week 4 and 8 in online assessments. Follow-up visits for all patients who want to use MSDeprexis after 6 and 12 month are conducted online.

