**MS-specific DeprexisPlus (guided version):** This group will receive the web-based Deprexis program, in its modified version to increase suitability for MS patients, plus scheduled e-mail contact with a therapist. The manual for the e-mail support will be based on a manual developed for the IDEMS trial (see appendix). The manual aims to maximize the e-mail support's suitability for the needs and requirements of MS patients. Experiences from recent projects in which detailed clinician manuals for Deprexis support conditions have been developed will also be considered in the protocol modification (<http://www.e-compared.eu/research/trials-design/>). The basic structure of the e-mail support will be as follows (based on (25)): At the beginning of the treatment, a therapist will introduce herself (or himself) via e-mail, which will be integrated (secure webmail) into the online study platform. Participants will be informed that they can contact their therapist whenever they want to. Once a week, the therapist will write a short e-mail with feedback based on participants' program usage over the previous week (i.e., as in previous studies with the supported Deprexis version, the therapists will be able access information regarding which modules the participants have engaged with and for how long). This feedback will also acknowledge participants' response to a brief mood measure and to the PHQ-9 (current depression), which they are asked to complete at regular intervals as they work through the program. Progress with the relevant Deprexis related tasks and specific therapeutic techniques, or principles can be briefly discussed in the e-mails, as well as MS-specific questions or concerns. The main function of this feedback is to encourage participants' independent work with the Deprexis program and to enhance engagement. Where there is no online activity by a participant, therapists will offer their help and assistance and will ask if the participant is facing any problem with the program or with the tasks. When participants ask a question, therapists will provide an answer 

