*Procedures implemented to control risk:* Acute risk for suicide at baseline (as determined by the SBQ-R, see above) will lead to exclusion from the trial and patients will immediately be referred to specialists for crisis intervention. In our previous trial (26) we found no evidence for the new occurrence of suicidal thoughts during the trial or at 6-months follow-up in the Deprexis or waitlist control group. Similarly, previous trials of Deprexis (including the recent trial of patients with severe depression (23)) also showed no evidence for increased suicidal ideation and intent. However, in the proposed trial we will establish a detailed protocol for detection and response to suicide risk. During the clinical visits, all patients will be asked about suicidal ideation and intent. In addition, we will obtain information about emergency contacts (friends/family) in a standardized manner. If participants express suicidality during their clinical visit, the site PI (neurologist or experienced clinical psychologist) will be contacted immediately by the study coordinator and will explore things further with them in person. If participants appear to present an immediate danger to themselves, then standard procedures established at each site will be followed for possible commitment. Participants will be informed in the informed consent form about the possibility that confidentiality may need to be breached if they express an immediate, serious danger to themselves. Finally, the secure online study platform will include a feature where helpline numbers will be automatically displayed if response on the BDI-II indicates suicide risk at any time (item 9 = 3). In this case, an automated email alert will also be sent to the study center of the patient for a follow-up phone call by the study coordinator and the site PI (neurologist or experienced clinical psychologist).

**Risk of blood sampling:** Blood sampling is considered low risk. Blood drawing from a vein may cause pain from insertion of the needle, light headedness, faintness, bruising, localized bleeding which may

look and feel like a bruise, and rarely inflammation of the vein, clotting of the vein and/or infection at the needle site.

*Procedures implemented to control risk:* Blood sampling will be conducted according to established protocols and performed by authorized personnel (study nurse or physician).

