#### **Serious Adverse Event - SAE**

Every AE fulfilling any of the following criteria is considered an SAE:

- Suicidal ideation or intent (as measured by a score of 3 on BDI-II item 9 at any assessment, during the clinical interview at V2 or spontaneous report in a web message to the therapist or by contacting the study site)
- Hospitalization due to psychiatric disorder classified according to ICD10 or DSM5
- Lethal or life-threatening (incl. suicide or suicide attempt)

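### Suicidality SAEs are tabulated by arm as one pooled count, although one of the four detection routes exists only in the guided arm and can inflate that arm's count

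*Supplement*

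**What the plan says.** The suicidality criterion is the same in SAP 5.4 (Harms) and in the SAE definition of protocol 9.1. It begins "Suicidal ideation or intent (as measured by a score of 3 on BDI-II item 9 at any assessment, during the clinical interview at V2" and goes on to "spontaneous report in a web message to the therapist or by contacting the study site". That makes four routes: BDI-II item 9, the V2 interview, a message to the therapist, and contact with the site.

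Only one arm has a therapist. Protocol 5.1 gives the guided arm the program "plus scheduled e-mail contact with a therapist", and the therapist manual's introduction describes staff "providing web message support to participants in the respective condition of the trial". In that arm, "Once a week, the therapist will write a short e-mail with feedback based on participants' program usage over the previous week", and participants are told that they may write at any time. No comparable correspondent is described for the other two arms.

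On tabulation, SAP 5.4 says: "Adverse events will be summarized as frequencies and percentages by intervention group". It does not split events by route. Protocol 9.2 lists what an AE record must hold (type, timing, intensity, causality), and how the event was found is not among them.

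The other routes are shared. Besides the clinic assessments at weeks 0 and 12, SAP 2.7 states: "In addition, BDI-II outcomes are measured at week 4 and 8 in online assessments". Protocol section 7 adds that "helpline numbers will be automatically displayed if response on the BDI-II indicates suicide risk at any time (item 9 = 3", with an alert to the study centre, and that every patient is asked about suicidality at the clinical visits. Separately, SAP Table 1 names the SBQ-R at V1 and V2 as the safety endpoint, and SAP 5.2 models it in the same way as the primary endpoint.

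**The concern.** An event count by arm can be read as a comparison of risk only if events are looked for in the same way in each arm. Here one arm has an extra, invited channel through which a patient can disclose suicidal thoughts, and a disclosure made there counts as an SAE. The same thoughts in a stand-alone or waitlist patient are counted only if they show at a scheduled assessment or the patient contacts the site.

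The pooled frequency therefore mixes occurrence with ascertainment. A modest excess in the guided arm could come from the extra channel alone, and similar counts could hide fewer true events there. Because the source is not recorded, nobody reading the table afterwards could separate the two. The count also has an audience during the trial: under protocol 9.4 the data monitoring committee looks at how often SAEs occur and how severe they are, and neither document sets a stopping rule. The documents do not say whether the committee sees the counts by arm.

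**Working it through.** The documents give no figure for this point, so there is no stated result to reproduce. The one design figure used is the arm size. SAP 2.3 takes 100 evaluable patients per arm and 20% dropout: 100 / (1 − 0.20) = 125 recruited per arm, which agrees with the plan.

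**Routes side by side**

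| Route | Guided | Stand-alone | Waitlist |
|---|---|---|---|
| BDI-II item 9 = 3 (weeks 4, 8, 12) | yes | yes | yes |
| V2 interview | yes | yes | yes |
| Contact with the site | yes | yes | yes |
| Message to the therapist | yes | no | no |

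**Model.** Let the true risk p be the same in all arms. Let s be the share of events found by the scheduled routes in every arm. Let m be the share of the remaining events found by therapist messages, in the guided arm only. Site contact has no separate term; if it finds the same share in each arm, it can be read as part of s. The documents give no values for p, s or m, so all three are assumptions shown over a range.

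- Expected count in each other arm: 125 × p × s
- Expected count in the guided arm: 125 × p × [s + (1 − s)m]
- Ratio: [s + (1 − s)m] / s, which does not depend on p

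| s | m = 0 | m = 0.25 | m = 0.50 |
|---|---|---|---|
| 0.8 | 1.00 | 0.85/0.80 = 1.06 | 0.90/0.80 = 1.125 |
| 0.5 | 1.00 | 0.625/0.50 = 1.25 | 0.75/0.50 = 1.50 |
| 0.3 | 1.00 | 0.475/0.30 = 1.58 | 0.65/0.30 = 2.17 |

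**In events.** With p = 2%, s = 0.5 and m = 0.5, each other arm expects 125 × 0.02 × 0.5 = 1.25 events and the guided arm expects 125 × 0.02 × 0.75 = 1.88. With binomial counts, the chance that the guided arm has strictly the highest count is 0.38, against 0.23 without the extra route. Over p = 1%, 2% and 5% and the s and m values above, that chance runs from 0.24 to 0.65, against 0.17 to 0.27 without the extra route.

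**After the change.** If only scheduled routes are counted, m = 0 and the ratio is 1.00 at every p and s.

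**The case against.** The case against giving this much weight is substantial, and most of it stands.

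- *The modelled safety comparison is elsewhere.* The SBQ-R is the named safety endpoint, is taken at the same visits in all arms, and does not draw on therapist messages. The AE table is descriptive, with no test. This is correct, so the point concerns one table and not the trial's main safety comparison. The SBQ-R is a scale score at two visits, however, and does not correct the SAE count.
- *Three of the four routes are shared.* This is also correct. Shared routes shrink the bias without removing it: at s = 0.8 the ratio is still 1.06 to 1.125.
- *The weekly e-mails are not assessments.* A reader might set about 12 weekly therapist contacts plus three scheduled assessments in the guided arm against three assessments elsewhere, and infer a fivefold difference in surveillance. The documents do not support that. The listed route is a message the patient chooses to send, whereas the weekly e-mails are outgoing feedback meant to encourage program use. The mood and PHQ-9 answers that the therapist sees are not a listed SAE source, and nothing says that stand-alone users do not complete them.
- *No excess was seen.* Supplementary Table 1 shows new suicidality of 0, 0 and 0 (control, stand-alone, guided), worsening of 3, 1 and 0, and other events of 6, 5 and 3. The guided arm has no excess in any row. This shows that no inflation appeared in this trial, but it does not make the planned tabulation sound.

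**Conclusion.** The concern holds in a limited form. Following the plan as written gives a suicidality SAE count with unequal ascertainment, and with equal true risk the extra route can raise the guided arm's expected count but cannot lower it. The size is unknown. A ratio of 1.06 to 2.17 follows if scheduled routes find 80% to 30% of events and messages find 25% to 50% of the rest, and none of those shares comes from the documents.

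A reader might infer that the guided arm is bound to look the least safe. That does not follow: this is a possible upward bias on very small expected counts, and over the assumed ranges the guided arm often would not have the highest count. Nor does the point reach worsening of depressive symptoms, because the message route is listed only for suicidality. The primary analysis and the SBQ-R analysis are unaffected.

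**What to change.** Record the first detection source of each suicidality event: BDI-II item 9, V2 interview, therapist message, or site contact. Then in SAP 5.4:

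- Keep the table of all events by arm.
- Add a by-arm table limited to the scheduled routes common to all arms (BDI-II item 9 = 3 at weeks 4, 8 and 12, and the V2 interview), and name it as the one for between-arm comparison. A patient positive at one of these assessments counts there even if a message came first.
- List all spontaneous reports separately by source, with therapist messages and site contacts together. Site contact should not stay in the comparison table while messages are left out: guided patients may tell the therapist instead of the site, and that split would undercount the guided arm.
- Flag any patient whose event was first found spontaneously and who then missed later scheduled assessments. The protocol synopsis lists clinically relevant suicidal ideation among the obligatory reasons for ending participation, so such a case may never reach the common assessments.

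Leave worsening events as they are. Reporting routes and clinical responses do not change.

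The cost is one source field and a few sentences in SAP 5.4. Data collection had begun when the SAP was written (section 5.3 already reports five missing online baselines), so the field may need retrospective coding. The common-route table will also rest on fewer events.

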## 5.5 Statistical software

Statistical programming will be done using R version 4.0.0 or higher and SAS version 9.4 or higher.

**Abbreviations**

|       |                                            |
|-------|--------------------------------------------|
| AE    | Adverse Event                              |
| CBT   | cognitive behavioral therapy               |
| ICBT  | internet-based CBT                         |
| SAE   | Serious Adverse Event                      |
| SUSAR | Suspected Unexpected Serious Adverse Event |
| ITT   | Intent to treat Population                 |
| PPP   | Per protocol population                    |
| RCT   | Randomized controlled trial                |
| WLC   | waitlist controls                          |

## 1 Synopsis

|                               |                                                                                                                                                                                                                                                                                                                                                                                                                                                                                                                                                                                                                                                         |
|-------------------------------|---------------------------------------------------------------------------------------------------------------------------------------------------------------------------------------------------------------------------------------------------------------------------------------------------------------------------------------------------------------------------------------------------------------------------------------------------------------------------------------------------------------------------------------------------------------------------------------------------------------------------------------------------------|
| Study Title            | International Deprexis Trial in Multiple Sclerosis (IDEMS) – a multi-center randomized controlled trial                                                                                                                                                                                                                                                                                                                                                                                                                                                                                                                                          |
| Type of Study          | Randomized controlled trial                                                                                                                                                                                                                                                                                                                                                                                                                                                                                                                                                                                                                             |
| Coordinating Center    | Charité – Universitätsmedizin Berlin
NeuroCure Clinical Research Center (NCRC)
[name]
[contact]                                                                                                                                                                                                                                                                                                                                                                                                                                                                                                            |
| Principal Investigator | [name]. [name]
Responsible medical investigator at coordinating center:
[name]. [name]                                                                                                                                                                                                                                                                                                                                                                                                                                                                                                                                       |
| Hypotheses             | The online program “Deprexis” is effective in reducing depressive symptoms in patients with multiple sclerosis                                                                                                                                                                                                                                                                                                                                                                                                                                                                                                                                          |
| Rationale              | Depression is the most common comorbidity of MS. However, depression remains underdiagnosed and there are no treatments with proven effectiveness from large (phase III) trials. In addition, symptoms of MS such as mobility issues, cognitive impairment and fatigue make it difficult for MS patients to travel to and attend regular psychotherapy. Effective treatment options are therefore needed. The internet-based program “Deprexis” could facilitate access to treatment and has shown promise in a small monocenter study in Germany. The current trial will evaluate the effectiveness of Deprexis in an international multicenter trial. |
| IMP & Treatment    | a) Deprexis as stand-alone for 12 weeks
b) Deprexis with added email support for 12 weeks                                                                                                                                                                                                                                                                                                                                                                                                                                                                                                                                                            |
| Control                | Waitlist control                                                                                                                                                                                                                                                                                                                                                                                                                                                                                                                                                                                                                                        |
| Study design           | Three arm, randomized, controlled, multicenter trial                                                                                                                                                                                                                                                                                                                                                                                                                                                                                                                                                                                                    |
| Anticipated schedule   | Initiation of recruitment – February 2017
Closure of recruitment – February 2019
Closure of trial – September 2019                                                                                                                                                                                                                                                                                                                                                                                                                                                                                                                                |
| Number of participants | 375                                                                                                                                                                                                                                                                                                                                                                                                                                                                                                                                                                                                                                                     |
| Target Population      | Multiple sclerosis                                                                                                                                                                                                                                                                                                                                                                                                                                                                                                                                                                                                                                      |
| Inclusion Criteria     | 
 
- age <math>\geq 18</math>
 
- neurologist-confirmed diagnosis of MS
 
- self-reported depressive symptoms (BDI-Fastscreen <math>\geq 4</math>)
 
- fluent in German or English (depending on study site),
 
- willingness to engage in self-administration of an iCBT intervention for 12 weeks and complete follow-up
 
- ability to travel to the outpatient center for two clinical assessments (baseline and week 12)
 
- internet access at home
 
- informed consent by patient
 
                                                               |
| Exclusion Criteria     | 
 
- unwilling or unable to consent,
 
- diagnosis of bipolar or psychosis (as determined by M.I.N.I structured interview),
 
- substantial neurocognitive impairments such as dementia or autism
 
- moderate or high risk of suicide (according to MINI module C) or by clinical impression
 
                                                                                                                                                                                                                                                                                       |

|                                                                                              |                                                                                                                                                                                                                                                                                                                                                                                                                                                                                                                                                                                                                                                                                                                           |
|----------------------------------------------------------------------------------------------|---------------------------------------------------------------------------------------------------------------------------------------------------------------------------------------------------------------------------------------------------------------------------------------------------------------------------------------------------------------------------------------------------------------------------------------------------------------------------------------------------------------------------------------------------------------------------------------------------------------------------------------------------------------------------------------------------------------------------|
|                                                                                              | 
 
- very severe depression that would interfere with the ability to participate in the study (based on clinical judgment by the physician at the recruitment site). Patients with very severe depression will be referred to psychiatric services for immediate treatment.
 
- current psychotherapy/behavioral treatments for depression
 
- started pharmacotherapy for depression within the last 2 months
 
- MS relapse or steroid treatment in the last 4 weeks
 
- concurrent participation in another interventional clinical trial
 
- Refusal to saving, processing and forwarding of pseudonymized data
 
                     |
| Visits                                                                                | 
Clinical visits:
Baseline and Week 12
 
Online questionnaires:
Month 6 and Month 12
                                                                                                                                                                                                                                                                                                                                                                                                                                                                                                                                                                                                                   |
| Endpoints                                                                             | 
 
• Primary endpoint: Beck Depression Inventory - II
 
• Secondary endpoints: 
 
○ WHO-QoL BREF
 
○ Multiple Sclerosis Impact Scale, MSIS-29
 
○ Fatigue Scale for Motor and Cognitive Functions (FSMC)
 
○ Chalder Fatigue Scale
 
○ Current MDD diagnosis (M.I.N.I. structured clinical interview, clinician-rating, version 5.0.0)
 
○ Montgomery Asberg Depression Rating Scale (MADRS)
 
 
 
• Safety and moderators 
 
○ Suicidal Behaviors Questionnaire-Revised
 
○ Brief Cognitive Assessment in MS (BICAMS)
 
 
 
 |
| Safety                                                                                | Documentation of adverse events with every visit.
SOP suicidality                                                                                                                                                                                                                                                                                                                                                                                                                                                                                                                                                                                                                                                      |
| Criteria for Discontinuation                                                          | 
Of Participation for an Individual:
Obligatory: Personal decision of the individual, potential harm (occurrence of clinically relevant suicidal ideation or at the discretion of the investigator)
Possible: Retrospectively assessed exclusion criterion
Severe Adverse Event (SAE) or Suspected Unexpected Serious Adverse Reaction (SUSAR)
 
Of the trial itself:
Change of the risk-benefit-analysis
                                                                                                                                                                                                                                                                        |
| Statistical Evaluation/Sample Size Calculation                                        | The primary outcome change in BDI from baseline to week 12 will be analyzed as intention-to-treat (ITT) by means of linear mixed effect models for repeated measures adjusted for baseline measurements including all patients with at least one post-baseline measurement. A sample size of 100 patients per intervention group gives a conjunctive power (probability of rejecting both null hypotheses comparing Deprexis and DeprexisPlus to waitlist control) of 90% for a Dunnett test at the usual one-sided significance level of 2.5%. Adjusting for 20% dropout we aim to recruit 125 patients per group resulting in a total sample size of 375 patients.                                                      |
| Pharmacological-toxicological Evaluation                                              | N/A                                                                                                                                                                                                                                                                                                                                                                                                                                                                                                                                                                                                                                                                                                                       |
| Possible Risks, Adverse Reactions, Contraindications, Procedures in case of incidents | The intervention is generally considered low risk as Deprexis has been used in numerous clinical trials without evidence for adverse events and is categorized as a “low risk” medical device according to                                                                                                                                                                                                                                                                                                                                                                                                                                                                                                                |

|                              |                                                                                                                                                                                                                          |
|------------------------------|--------------------------------------------------------------------------------------------------------------------------------------------------------------------------------------------------------------------------|
|                              | its German CE®-certification. We will exclude patients with more than a low risk of suicidality. Standard operating procedures are in place to respond to occurrence of suicidal thoughts and intent in any participant. |
| Risk-Benefit-Analysis | Risk-benefit ratio is considered acceptable as risk is low but patients may benefit from a new online intervention tool to reduce depressive symptoms.                                                                   |

